# Multicentric randomized clinical trial to evaluate the long-term effectiveness of a motivational intervention against smoking, based on the information obtained from spirometry in primary care: the RESET study protocol

**DOI:** 10.1186/s12875-016-0415-1

**Published:** 2016-02-04

**Keywords:** Spirometry, Tobacco smoking, Motivational intervention, Primary health care

## Abstract

**Background:**

Spirometry is the recommended method of evaluating pulmonary function when respiratory disease is suspected in smokers. Nonetheless, no evidence exists of the usefulness of information obtained from this test as a motivational strategy for smoking cessation. The primary objective of this study is to evaluate the effectiveness of a motivational intervention based on spirometry results in achieving long-term smoking cessation.

**Methods/Design:**

We propose a multicenter randomized clinical trial in the primary care setting. **Study subjects**: We will recruit active smokers of both sexes, aged 35-70 years, with a cumulated smoking habit exceeding 10 packs/year and who consult for any reason with their primary care physician in the 20 health centers in the province of Tarragona (Spain). Patients with a history of lung disease or who have undergone exploratory measures of pulmonary function in the preceding 12 months will be excluded. All patients who agree to participate will provide signed informed consent prior to their inclusion. A total of 1000 smokers will be consecutively randomized to a control or intervention group (1:1). **Intervention:** Participants in both groups will receive brief (5-minute) health counseling, in accordance with usual clinical practice. In a consultation lasting about 15 minutes, participants in the intervention group will also receive detailed, personalized information about the results of a spirometry test and about their lung age compared with their chronological age. Both groups will be followed up for 12 months. **Main variables and analysis:** The main variable will be sustained smoking abstinence at 12 months after the intervention, as confirmed by CO breath testing and urine cotinine test. Results will be analyzed based on intention to treat, using the chi-square test and logistical regression if necessary to adjust for confounding variables.

**Discussion:**

We expect the rate of prolonged smoking abstinence in the intervention group will be at least 5 % higher than in the control group. If this strategy proves effective, it could easily be included in the health promotion activities offered in primary care settings.

**Trial registration:**

ClinicalTrials.gov Identifier: NCT02153047. Registered on 28/05/2014

## Background

Diseases related to smoking frequently motivate patient visits to health care settings in general and primary care in particular. The magnitude of this health problem has been widely studied and has been cited as the primary preventable cause of mortality and morbidity in industrialized countries [1].

The available data indicate that the life expectancy of habitual smokers is reduced by 15-20 years and approximately half will die as a consequence of their habit [2]. Taking this into account, it is surprising that the detrimental health effects of smoking have so little social impact and that smoking continues to be highly prevalent in our context [3]. The health benefits of smoking cessation are well established. With few exceptions, future risk is reduced when smokers stop smoking and continue to decrease while smoking abstinence is maintained. Progression of smoking-related diseases is also slowed and life expectancy improves by an average of 10 years [2]. For these reasons, anti-smoking efforts in all contexts provide one of the major central points around which many disease prevention strategies revolve [3].

Treatment of the effects of smoking is an important part of clinical practice and all health professionals need to offer help and support to all smokers as part of usual clinical practice [4]. Current guidelines base their recommendations on the “The 5As approach” (ask about tobacco use, advise to quit, assess willingness to make a quit attempt, assist in quit attempt, and arrange follow-up) [5]. According to this model, the health professional who knows the smoker’s motivation can choose the strategy that has shown the greatest effectiveness in each situation. Nonetheless, cigarette smoking is a highly addictive habit that is difficult to give up, and achieving the motivation to quit smoking is always a challenge. The available data suggest that the majority of smokers are interested in quitting [6] and that structured counseling by health care professionals is a motivational element for smoking cessation [7]. However, the rate of successful quit attempts is low and does not usually exceed 10 % [8]. To increase the success rate and accelerate change in smoking habits, it has been suggested that instead of providing patients with general information about the detrimental heath effects of smoking, they should be provided with personalized data on their risk of acquiring a disease related to smoking [9].

Health concerns are among the reasons most often cited as catalysts for smokers to make an attempt to quit smoking [10, 11], and studies suggest that the more a patient is aware of risks and benefits, the greater is their motivation and likelihood of success [12]. Similar to what occurs in smokers who have experienced smoking-related complications, providing information about testing for smoking-related harm or risks to health offers a “teachable moment” that may facilitate behavioral change [13]. In this respect, we can conceptually distinguish three different feedback methods, depending on the approach used to assess risk [14]: the first explores biomarkers of tobacco exposure, such as levels of urine cotinine or exhaled carbon monoxide (eCO); the second gives information about added risk of diseases related to a smoking habit, such as genetic susceptibility to lung cancer; and the third focuses on smoking-related harms such as the presence of arterial plaque detected by echography or decreased pulmonary function quantified by spirometry.

Spirometry is the recommended method of testing pulmonary function to detect restricted respiratory flow in smokers susceptible to chronic obstructive pulmonary disease (COPD) [15]. The use of spirometry has become generalized in primary care because it is a simple, noninvasive procedure that provides valuable information about pulmonary function and risk of premature death [16, 17] that can increase motivation to quit smoking [18]. Some years ago, the Lung Health Study showed that significantly more participants included in an intensive smoking cessation program quit smoking, compared to those included in the usual program [19]. Nonetheless, the experts involved in the most recent report published by the U.S. Preventive Services Task Force did not find sufficient evidence to conclude that the use of spirometry improved rates of smoking abstinence or affected the management of the initial stages of COPD [20].

In recent years, various clinical trials have explored the effect on smoking cessation of providing feedback on spirometry results. The first study, published by Segnan et al [21], included 923 smokers recruited by 44 primary care doctors in Italy. Participants were randomly assigned to 4 different intervention groups: (a) a brief individual intervention, (b) an intensive intervention with 4 follow-up sessions, (c) an intensive intervention and treatment with nicotine gum, and (d) an intensive intervention and spirometry. The proportion of exsmokers at 12-month follow-up was 4.8 %, 5.5 %, 7.5 %, and 6.5 %, respectively, with no significant differences between the groups (RR: 1.19; 95 %CI: 0.62-2.30). Later, Buffels et al [22] published a study that included 215 smokers attending 14 primary care centers in Belgium who were prescribed treatment with nicotine, bupropion, or both and were randomly assigned to receive only a minimal intervention or the intervention along with information about their spirometry results. After 12 months of follow-up, a nonsignificant effect in favor of the spirometry intervention was observed (RR: 1.17; 95 %CI: 0.66-2.06). More recently, Parkes et al [23] published a clinical trial that included 561 smokers recruited in 5 primary care centers in England. All participants were assessed using spirometry and then randomized to receive personalized information about the results obtained, summarized as “lung age” compared to chronological age (intervention group), or to receive a letter reporting the results (control group). After 12 months of follow-up, the rates of punctual smoking abstinence were significantly higher in the intervention group (13.6 % vs 6.4 % in the control group, *p* = 0.005) and these participants had higher probability of successful smoking cessation than those who did not receive personalized spirometry results (RR: 2.12; 95 %CI: 1.24-3.62). Nonetheless, the observed abstinence rate could have been influenced by the intensity of the intervention that was administered (longer period of contact in the intervention group due to verbal reinforcement); it has been shown that abstinence rates are directly proportional to the intensity of the strategy used [24].

In a Cochrane Database of Systematic Reviews article, Bize et al evaluated those three studies and 12 other clinical trials that have used various biomarkers as a motivational strategy for successful smoking cessation [25]. Unfortunately, the designs of the studies included in the review were so heterogeneous that only two pairs of studies were sufficiently similar in methodology and intervention to allow a combined analysis. The authors also found no evidence of significant benefits from the use of eCO measurement or spirometry in primary care to improve success rates for smoking cessation efforts. Therefore, they conclude that, due to the lack of quality evidence, it is not possible to establish definitive recommendations about the effectiveness of most approaches used to evaluate biomedical risk assessment as a means of helping smokers quit smoking. They emphasize a need to improve the methodological quality of future studies. Their review included two active clinical trials with similar methodology, ESPIROTAB and ESPITAP [26, 27], that use spirometry results as a motivational strategy to increase smoking cessation success rates beyond the levels obtained by usual counseling, as in the study by Parkes et al [23]. Nonetheless, this type of study design has been criticized because, strictly speaking, it does not provide independent evidence of the effectiveness of using spirometry, compared to no spirometry; this would require a trial in which spirometry is not used in the control group [28].

The use of spirometry as a motivational tool for smoking cessation continues to be a controversial topic. Some data indicating effectiveness are encouraging, but the scarcity of evidence limits the capacity to establish definitive recommendations about its use.

For all these reasons, further studies are essential, and must use high-quality methodology with a sufficiently large sample and long-term follow-up of at least 12 months to establish a final outcome of prolonged smoking abstinence, confirmed by a biochemical method [25].

## Hypothesis and objectives

### Hypothesis

An intervention based on providing structured, standardized information about the results of spirometry as part of usual clinical practice to encourage patients to quit smoking will achieve improvement of 5 % or more in the rate of prolonged abstinence from smoking at 12 months of follow-up, compared to that obtained by providing only the usual brief counseling to patients who smoke.

### Objectives

The primary objective of this study is to evaluate the effectiveness of providing structured information about the results of spirometry testing to increase the rate of prolonged abstinence from smoking at 12 months after an anti-smoking intervention in primary care patients who smoke but do not have a known respiratory disease.

## Material and methods

### Design

The general framework of the RESET study is shown in Fig. 1 and the activities to be carried out at each visit are detailed in Table 1. This is the second phase of the ESPITAP study (Spanish acronym for “Effectiveness of Smoking Cessation Advice Combined With Spirometric Results in Adult Smokers”), a randomized, controlled, parallel, multicenter clinical trial in smokers with no history of respiratory disease, recruited when they visited a primary care center [27].

**Fig. 1 Fig1:**
[figure not shown]
Diagram of the RESET study: process of selection, randomization and follow-up of subjects included in the study

**Table 1 Tab1:** Diagram of activities to be carried out by participants at each visit

	Visit 0	Visit 1	Visit 2	Visit 3	Visit 4
	Selection Inclusion Randomization	Intervention	Follow-up Reminder Intervention	Follow-up Reminder Intervention	End of study
Timeline	Day -30 to -1	Day 0	3 months	6 months	12 months
Procedures					
Informed Consent	X				
Sociodemographic data	X				
Personal history	X				
Basic physical examination	X				
Smoking habit and coximetry	X				
Randomization	X				
Spirometry	X				
Intervention					
Control group: brief health counseling		X			
Intervention group: brief health counseling + information about spirometry results		X			
Measures of effectiveness					
Smoking habit			X	X	X
Confirmation of smoking abstinence (coximetry and urine cotinine)					X

### Setting and study population

The study population will be obtained from patients who consult any primary care center managed by the Catalan Institute of Health in the province of Tarragona. These 20 centers, 12 urban and 8 rural, employ 286 family doctors who care for an adult population (older than 18 years) of 279,637 patients.

### Participant selection

Eligible participants include all patients aged 35 to 70 years who smoke, who consult their primary care team during regular office hours for any reason during the inclusion period, and who meet all inclusion criteria and none of the exclusion criteria, as follows:Inclusion criteria: active cigarette smoker with a cumulative habit of more than 10 packs/year. An active smoker is defined as one who acknowledges having smoked regularly during the past 30 days, regardless of the quantity. Cumulative consumption (pack-years) is defined as the value obtained by multiplying the daily mean of cigarettes smoked by the number of years as a smoker, divided by 20 cigarettes/pack.Exclusion criteria:Any evidence of previous respiratory disease diagnosis (e.g., COPD, chronic bronchitis, asthma, bronchiectasis, etc.).Pulmonary function examination within previous 12 months,Any chronic or terminal disorder that, in the researcher’s opinion, could affect the baseline parameters or the tests required for the study,Impossibility of follow-up participation for any reason, andPatient refusal to participate or withdrawal from the study.

### Sample calculation

To achieve the study objective, a sample of 1000 participants, 500 in each study group (control and intervention), will be recruited. This will allow the detection of differences in smoking abstinence greater than or equal to 5 %, with 95 % CI and 80 % strength in two-tailed tests, assuming an abstinence rate of 5 % to 6 % in the control group at 12 months and approximately 10 % loss rate during follow-up [24].

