#### Randomization

After the selection visit, included participants will be randomized 1:1 to the intervention or control group. The group assignment will be blinded, consecutive, and centralized at the Tarragona Research Support Unit of the IDIAP Jordi Gol, and will follow a simple randomization numeric sequence compiled for this purpose. Of course, due to the nature of the intervention, researchers and participants cannot be blinded to this assignment.

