To evaluate the effectiveness of the smoking cessation intervention, rates of punctual and prolonged abstinence were assessed at 12 months post-intervention in both groups using the chi-square test. The results were presented as relative risk (RR), relative risk reduction (RRR) and absolute risk reduction (RAR) and number needed to treat (NNT) to achieve prolonged smoking abstinence in one smoker, expressed with their 95 % confidence interval (CI). To study the behavior of both groups over time, log-rank tests were used to compare the cumulated abstinence curves over the 12-month follow-up. Finally, multivariate analysis using Cox regression was applied to study the factors associated with smoking cessation success at 12 months. Various models were formulated that included the variable of interest (the described interventions) and as control variables the factors shown to be most significant in the literature [38]: age, sex, social class, employment status, educational level, daily and cumulated tobacco use, degree of nicotine dependence, degree of motivation to quit smoking, and stage of change.

All analysis was done using SPSS version 19.0. Significance was set at *p* < 0.05.

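### The stated 80% power for a 5-point difference does not hold at the 6% upper end of the assumed control rate; after the stated 10% loss it is about 77% there

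*Protocol article*

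**What the plan says.** All the inputs are in the protocol article. Under Sample calculation, "a sample of 1000 participants, 500 in each study group (control and intervention), will be recruited". This number is said to allow "detection of differences in smoking abstinence greater than or equal to 5" percent, "with 95 % CI and 80 % strength in two-tailed tests". Two further assumptions follow: "assuming an abstinence rate of 5 % to 6 % in the control group at 12 months", and "approximately 10 % loss rate during follow-up". The section gives no formula and does not say which control rate within the range fixed the sample size.

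The Randomization section confirms equal allocation: "included participants will be randomized 1:1 to the intervention or control group". The Statistical analysis section names the test for the primary outcome: "rates of punctual and prolonged abstinence were assessed at 12 months post-intervention in both groups using the chi-square test".

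**The concern.** The section attaches one power figure to a range of control rates. For a fixed absolute difference at rates this low, the binomial variance rises with the control rate, so power is lowest at the top of the range. A claim made for the whole range has to hold at 6%, and a sample size that just suffices at 5% need not.

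What is at stake is how a result near the margin will be read. The Hypothesis section uses the same 5-point improvement as its target. If the trial does not show a difference, readers will rely on the stated 80% to judge how firmly a 5-point effect has been excluded. They should know that the figure weakens towards the upper end of the range.

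**Working it through.** **Inputs** (from the sections cited above)

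- 500 randomized per arm, 1:1.
- Two-sided alpha 0.05 (read from the 95% confidence level and the two-tailed test), so z = 1.960; 80% power, so z = 0.8416.
- Control rate pC from 5% to 6%; intervention rate pT = pC + 5 points.
- Loss of about 10%: 500 × 0.9 = 450 evaluable per arm.
- Chi-square test of two proportions.

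**Formulas** (pooled variance under the null, p̄ = (pC + pT)/2)

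- Power = Φ[(0.05 − 1.960·SE0)/SE1], with SE0 = √[2p̄(1 − p̄)/n] and SE1 = √[(pC(1 − pC) + pT(1 − pT))/n].
- n per arm = [1.960·√(2p̄(1 − p̄)) + 0.8416·√(pC(1 − pC) + pT(1 − pT))]² / 0.05², then divided by 0.9 for loss.

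**Step 1: reproduce the plan's figure at 5% versus 10%, n = 450**

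- SE0 = 0.01756, SE1 = 0.01748.
- (0.05 − 0.03442)/0.01748 = 0.892, so power = 81.4%.
- Required: 434.4, rounded up to 435 evaluable; 435/0.9 gives 484 per arm, 968 in total. The plan's 1000 covers this.

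**Step 2: midpoint, 5.5% versus 10.5%, n = 450**

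- SE0 = 0.01809, SE1 = 0.01801.
- (0.05 − 0.03545)/0.01801 = 0.808, so power = 79.0% (0.7905).
- Required: 461 evaluable; 461/0.9 gives 513 per arm, 1026 in total.

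**Step 3: upper end, 6% versus 11%, n = 450**

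- SE0 = 0.01859, SE1 = 0.01852.
- (0.05 − 0.03644)/0.01852 = 0.732, so power = 76.8%.
- Required: 487.2, rounded up to 488 evaluable; 488/0.9 gives 543 per arm, 1086 in total.

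**Summary**

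| Control vs intervention | Power, 450 per arm (pooled) | Power, 450 per arm (exact, uncorrected chi-square) | Total N for 80% after 10% loss |
|---|---|---|---|
| 5% vs 10% | 81.4% | 82.1% | 968 |
| 5.5% vs 10.5% | 79.0% | 79.7% | 1026 |
| 6% vs 11% | 76.8% | 77.4% | 1086 |

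**Step 4: does the choice of method matter at 6%?** Unpooled variance gives 77.0% and the arcsine method 77.6%. If losses instead count as smokers and dilute both rates (6% × 0.9 = 5.4% and 11% × 0.9 = 9.9%, 500 per arm), power is 76.4%. All of these lie between 76% and 78%.

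**Step 5: where does the claim stop holding?** With 450 per arm, pooled power falls to 80% at a control rate of about 5.3%. At a 6% control rate, power reaches 80% at a difference of about 5.24 points, or 5.2 after rounding (exactly 5.2 points gives 79.6%).

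**The case against.** Three arguments on the other side deserve weight.

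*The inputs are round, so the output should be read as round.* The loss is approximate, the control rate is a range and 1000 is a round number. This stands at the midpoint: 79.0% (79.7% exact) is 80% for practical purposes, and a loss of 7.8% instead of 10% would leave the 461 per arm that are needed. A reader might infer that the claim already fails at 5.5%; inputs this coarse do not support that. The argument does not reach 6%, where the gap is about 3 points, or 86 participants.

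*The denominator might be 500.* The article commits to intention to treat. If 5% to 6% were a rate among all randomized participants, with those lost already counted as smokers, n would stay at 500 and power at 6% would be 81.0%, so the claim would hold throughout. But the Sample calculation section does not define the rate that way. It lists loss as a separate assumption, and the Statistical analysis section describes a comparison that leaves the lost participants out. The 450 reading is the more natural one, though it is not the only one possible.

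*The 5% end may have set the sample size, with 6% mentioned only as uncertainty.* That is possible, but the sentence does not say so and gives one power figure for the whole range.

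**Conclusion.** The point holds at the upper end of the range only. On the protocol's own inputs, the stated 80% power is met at a 5% control rate (about 81% to 82%), is within rounding at 5.5% (about 79% to 80%), and is not met at 6% (about 77%). This is a minor error in a stated figure, and the test and the analysis are unaffected. It rests on taking the 10% loss as a reduction to 450 evaluable per arm, or as dilution of both rates, and on a two-sided test at 0.05.

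Two stronger readings should not be drawn from it. First, a continuity-corrected chi-square gives lower power at 6% (73.5% exact). The article specifies no correction, and the corrected test also falls below 80% at 5% (78.5%), so that figure reflects the choice of test and says nothing about the control-rate range. Second, a reader might infer from the advice, calls and clinic offers given to controls that 6% is the likelier rate. The article does not establish this: it describes control care as usual practice, and the earlier trials in its Background report 4.8% with brief intervention in one and 6.4% among controls in another.

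**What to change.** Keep the sample size at 1000 and replace the power statement under Sample calculation with wording such as: *With 450 evaluable participants per arm, power to detect a 5-point difference is about 81% if control abstinence is 5% and about 77% if it is 6%; at 6% the difference detectable with 80% power is about 5.2 points.* If the authors meant the control rate to apply to all randomized participants with losses counted as smokers, they should say so and drop the separate loss allowance; the figure at 6% is then 81.0%.

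The cost is one sentence and a slightly less favourable power figure. No participants are added, and the design and the analysis do not change.
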